### Breakfast treatment

According to the Chinese Dietary Guidelines [22] and Chinese Dietary Reference Intakes [23] as well as the food taboos and preferences of the participants [24], three types of breakfast will be prepared: a nutrition-adequate breakfast, a nutrition-inadequate breakfast, and no breakfast. The energy and nutrients of the nutrition-adequate breakfast and the nutrition-inadequate breakfast are shown in Table 1.

**Table 1 Tab1:** Energy and nutrients from the nutrition-adequate breakfast and nutrition-inadequate breakfast

	Nutrition-adequate breakfast		Nutrition-inadequate breakfast	
	Male	Female	Male	Female
Food				
Congee (g)	200	200	200	200
Steamed bread (g)	120	80	60	30
Bean curd (g)	40	30	0	0
Eggs (g)	50	50	50	50
Beef (g)	40	30	0	0
Vegetables (g)	120	120	120	120
Fruits (g)	80	80	0	0
Macronutrient				
Protein (g)	17.9	12.9	8.3	9.3
Fat (g)	10.9	10.6	6.7	6.7
Carbohydrates (g)	126.4	90.4	87.1	73.5
Energy (kcal)	670	540	330	270

The nutrition-adequate breakfast will be composed of grains, animal protein (meat, eggs), soy products, vegetables and fruits, and it will provide energy to meet the requirements of 18- to 49-year-old adults who engage in light physical activity. The nutrition-adequate breakfast will provide 675 kcal (2250 kcal × 30%) for males and 540 kcal (1800 kcal × 30%) for females.

The nutrition-inadequate breakfast will provide half the energy of the nutrition adequate breakfast. The energy from the nutrition-inadequate breakfast will be 330 kcal for males and 270 kcal for females.

Participants in the no breakfast treatment will not eat breakfast. Therefore, they will ingest 0 kcal at breakfast.

### Cognitive function tests

The cognitive function tests will consist of short-term memory, learning and memory, and attention tests, which have been used to detect differences in cognitive function induced by glucose administration in previous studies [8, 20, 25]. Cognitive function tests will be administered in the same order to each participant for the three weekly testing times: (1) Mood, (2) Hunger and satiety, (3) Short term memory, (4) Learning and memory, and (5) Attention.

It is anticipated that the test duration time will be approximately 30 minutes.

#### Mood

The self-reported mood questionnaire that will be used was developed from the Positive Affect and Negative Affect Scale (PANAS) [26]. It was modified from previous research for Chinese adults. Twenty words will be used to assess mood [27]. All responses on a 5-point scale ranging from “not at all” to “extremely” will be analysed.

#### Hunger and satiety

Hunger and satiety data will be obtained to determine whether the observed effects are associated with changes in hunger or satiety. Sense of hunger and satiety will be assessed by using Stunkard’s method [28]. Standardized instructions and paper visual analogue scales (0–100 mm) will be used. A visual analogue scale will be provided that will display a construct so that its extreme left edge will represent the absence of the characteristic (e.g., no hunger at all or no feeling of fullness). The extreme right side of the construct will represent the highest possible degree of the characteristic, which, in this particular case, will be the greatest intensity of hunger imaginable. If satiety is being measured, this edge will indicate complete or maximum satiety. Participants will be instructed to place a vertical line through the horizontal axis, with the distance from the left edge corresponding to the current degree of hunger and satiety on the provided scale that encompasses a spectrum ranging from zero (not present) to the maximum (highest level), from the left edge to the right edge.

#### Short-term memory

A “digit span” task will be used to assess short-term memory. The participants will be instructed to listen and repeat what they hear. For example, if the investigator says “1 2 3”, the participant will repeat “1 2 3”. Words will be presented at a rate of one word per second. After a correct repetition by the participant, the next set of numbers will be increased by one. If the participant does not repeat the numbers correctly, the investigator will provide another set of words of the same length to the participant. Two incorrect repetitions will result in the termination of the test. Each participant will receive both a forward and a backward version of this task. The backward version will require the subject to repeat the numbers in reverse order. Thus, in continuing with the above example, the participant will repeat “3 2 1”. A total score (forward recall + backward recall) will then be used to assess overall paragraph recall performance.

#### Learning and memory

Learning and memory will be assessed by using the digit-symbol coding method, which mainly measures digital decoding ability, visual memory, visual attention and operating speed. A continuous performance task will be used to evaluate attention, through focusing on the vigilance component of attention. This task’s evaluation will consist of providing, for example, nine digit-symbol pairs (e.g., 1/一, 2/丄, 3/], 4/□, 5/∪, 6/○, 7/Λ,8/X,9/=) followed by a list of digits. Under each digit, the participant will be instructed to write down the corresponding symbol as quickly as possible. The number of correct symbols within the allotted time will be measured (90 seconds). The test results will provide an indicator of speed during involvement with activities such as visual search, attention, mental flexibility, and motor function.

#### Attention

A table composed of eight letters (A, B, C, E, H, K, N, X) will be provided, and participants will be asked to remove a specified letter under specific conditions. For example, participants will be asked to delete B, which follows H (with the suppression condition of Aventura Karimov lettering). In the provided tables, each letter will appear 150 times, and 1200 letters will be provided. The test time will be 2 minutes, and each test will use the same alphabet. Before performing the test, the investigator will explain the test’s rules. The reading velocity, mistake rate, index of mental capacity (IMC) as measured by the Number Cancellation Test and test time, and correct number of tracking lines as measured by the Visual Tracking Test will be calculated.

#### Creativity

Four types of description words, such as “usually red”, “usually round”, “usually noisy” and “usually with wheels”, will be provided. Within 5 minutes, participants will be asked to list as many different items as possible that fit the above descriptions. For example, the description “usually blue” can be expected to be associated with the sea, a fountain pen, the colour of water, or blue jeans, all of which are commonly associated with the colour “blue”.

#### Language logic

Language logic involves a series of logical presentations of right and wrong. For example, “a is in front of b” means that a and b or ab are the correct sequences. In such cases, the answer is right. However, in this context, the statement that “b is not behind a” means that an answer of “a and b” in this case would be scored as wrong, as the answer is erroneous.

The logical test results (i.e., the completed and the correct number of responses) will be evaluated. They will be defined as:$$ \operatorname{Completed} \operatorname {number} = \operatorname{number} \operatorname {of} \operatorname {completed} \operatorname {questions} \operatorname {in}\ 3 \operatorname {minutes} $$
$$ \operatorname{Correct} \operatorname {number} = \operatorname{the} \operatorname {correct} \operatorname {number}/\operatorname{the} \operatorname {completed} \operatorname {number} $$

### Study procedure

Each participant from each of the three groups will receive the designated breakfast and complete the tests for three successive weeks, and the order of presentation will be counter-balanced across the groups. All participants will be instructed to fast from 20:00 pm the night before the study. The next morning, the participants will arrive at the designed location at 07:30 am. All the participants will rest in a seated position for 10 minutes and provide a finger-prick blood sample for the blood glucose test (blood glucose meter, Roche ACCU-CHEK®-Performa). Subsequently, participants from the groups that consume a nutrition-adequate and a nutrition-inadequate breakfast will have 15 minutes to ingest their breakfast in the designed location under the supervision of investigators until the breakfast is completely eaten. The breakfast will be delivered by the investigators. During this interval, the participants in the no breakfast treatment group will rest for 15 minutes. After 120 minutes, a second finger-prick blood sample from each participant for the blood glucose test will be collected. Then, all the participants will complete a series of tests on mood, sense of hunger and satiety, and cognitive function. All the tests will be performed under similar laboratory conditions (quiet room, 22–24 °C). Testing will not occur on Mondays, because the diets of the participants over the weekend is likely to be more varied than usual and, in the case of poorly nourished participants, lower in energy intake. The study procedure is shown in Fig. 2.

**Fig. 2 Fig2:**
[figure not shown]
The study process

### Quality control

A study manual will be provided before the survey, and one training will be conducted for all the investigators in the two cities. With the appropriate implementation and application of the unified method, a standardized face-to-face questionnaire will be administered.

Standardized experimental equipment and measurement methods will be used in the two cities to enable easy data interoperability. In addition, to ensure the same composition and quality of the breakfasts, the two cities will use the same breakfast recipes.

The data will be collected and entered by trained staff members from the Liaoning Center for Disease Control and Prevention and Chongqing Medical University. Double entry will be performed, and the data will be compared to identify and correct any discrepancies.

### Data management and entry

All the questionnaires will be collected, stored in a single file and regularly checked and rechecked. The questionnaires will be encoded and entered in a timely manner with the use of the Epidata 3.1 double entry test results.

### Analysis strategy

Statistical analyses will be conducted using SAS 9.2 (SAS Institute Inc., Cary, NC). Descriptive statistics will be calculated for all the variables under examination. Anthropometric measurements at baseline will be analysed to examine the influence of the factors on breakfast behaviour by using multivariate regression analysis, with age, sex, income and education level included in the model. Repeated-measures analysis of variance (ANOVA) will be used to examine cognitive function performance, with breakfast condition (Group A, Group B, or Group C) as the within-subjects variable and sex as the between-subjects variable. Significant confounding variables (in addition to gender), including satiety, mood score before the cognitive function tests, and time between breakfast and the first cognitive function test, will all be included initially as covariates in the two-way ANOVA. The significance level will be set at <0.05. The Bonferroni adjustment method will be used to perform the pairwise comparisons across different breakfast types. The significance test level will be ɑ' = 0.01667 (0.05/3). A modified t-test for gender differences will be used, and the significance level will be set at <0.05. All *P*-values will be two-tailed.

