## Discussion

According to the design of the experiment, all the participants will receive three breakfast treatments in different stages to determine whether differences in cognitive function exist among the different groups. This experimental design will ensure that there is a balance in the confounding variables in each group and will eliminate the bias caused by participants’ characteristics. In addition, to ensure consistency in the composition and quality of the breakfast conditions, the same breakfast recipes will be used in the two cities, and one breakfast company will be responsible for the production and the distribution of the different breakfasts. In addition, breakfast samples will be sent to the Chongqing Food and Drug Inspection Institute for the measurement of energy and composition.

One challenge that we will face in this study will be the dropout rate and participant compliance. Participants will need to be present for three consecutive weeks. Some participants might fail to complete the entire study because of business travel, tardiness, resignation and other reasons. We will fully explain the principles and requirements to the participants before the study begins to ensure compliance.

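### The three-week crossover model has no week (period) term, so any practice gain inflates the error and can bias the breakfast contrasts if dropout differs between sequences

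*Protocol article*

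**What the plan says.** The Analysis strategy section names a repeated-measures ANOVA "with breakfast condition (Group A, Group B, or Group C) as the within-subjects variable and sex as the between-subjects variable". The covariates for this two-way model are described as "including satiety, mood score before the cognitive function tests, and time between breakfast and the first cognitive function test". Pairwise comparisons between breakfast types are Bonferroni-adjusted, two-sided, at 0.05/3 = 0.01667. Week, period, order and sequence are not mentioned in the analysis.

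Under Participants and study design, each randomised group takes all three breakfasts, one per week, in three successive weeks. On repetition, the Cognitive function tests section says: "Cognitive function tests will be administered in the same order to each participant for the three weekly testing times". The digit-symbol task is scored over 90 seconds. The cancellation task lasts 2 minutes, and "each test will use the same alphabet". The Study procedure describes no practice session.

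The sample size section allows for 10% dropout, and the Discussion adds: "Some participants might fail to complete the entire study because of business travel, tardiness, resignation and other reasons".

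**The concern.** Timed tests repeated at weekly intervals are open to practice effects. The design anticipates order effects by counterbalancing the breakfasts over weeks, but the model does not carry that structure into the analysis. Two consequences follow.

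- **Precision.** Systematic differences between weeks that are not modelled are counted as residual variation. Standard errors are then too large and power is lost.
- **Bias.** Counterbalancing cancels the week effect only while the sequences contribute equal numbers. If more people are lost from one sequence than another, part of the practice gain remains in the breakfast contrasts.

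This model carries the trial's single stated hypothesis.

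**Working it through.** **The plan's own figures.** 117 / 0.9 = 130 per city. Three groups of 44 give 132, and two cities give 264, or 88 per sequence group. These reproduce. The 117 itself cannot be checked, because no SD or within-person correlation is given. With 10% loss, 264 × 0.9 = 237.6; I use 237 completers, 79 per sequence.

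**Assumption.** Mean practice gains at weeks 1, 2 and 3, in within-person residual SDs: 0/0.3/0.5 (mild), 0/0.5/0.8 (moderate) and 0/1.0/1.5 (large). The documents give no value, so these only show a range.

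**Step 1: error variance without week, equal sequences.** The factor is about 1 + Σ(pⱼ − p̄)²/2, where pⱼ is the gain at week j.
- Mild: p̄ = 0.267, sum of squares 0.127, factor 1.06.
- Moderate: p̄ = 0.433, sum of squares 0.327, factor 1.16.
- Large: p̄ = 0.833, sum of squares 1.167, factor 1.58.

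**Step 2: power and test size.** The contrast's true standard error is √(2/237) = 0.0919 SD. The critical value at two-sided 0.01667 is 2.394, and 80% power adds 0.842. The detectable effect is therefore 3.236 × 0.0919 = 0.297, about 0.30 SD. Omitting week leaves the estimate and its true variance unchanged and inflates only the estimated standard error. Power is then Φ(3.236 − 2.394 × √factor).
- Mild: Φ(3.236 − 2.469) = 78%.
- Moderate: Φ(3.236 − 2.582) = 74%.
- Large: Φ(3.236 − 3.012) = 59%.

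Under the null, the pairwise rejection rate 2 × [1 − Φ(2.394 × √factor)] falls from 0.0167 to about 0.014, 0.010 and 0.003. With week fitted, power stays at 80%.

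**Step 3: the same with 80% power set at 117.** The sample size section reaches its power with 117 in one city and then doubles recruitment. Pooling both cities multiplies 3.236 by √(237/117) = 1.423, giving 4.605. Power without week is Φ(4.605 − 2.469) = 98%, Φ(4.605 − 2.582) = 98% and Φ(4.605 − 3.012) = 94%; t quantiles bring the last to about 95%.

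**Step 4: bias with unequal completers.** Under Participants and study design, adequate falls in weeks 1, 2 and 3 for Groups A, B and C, and no breakfast in weeks 2, 3 and 1. Among completers without a week term, the bias in adequate minus none is [nA(p₁ − p₂) + nB(p₂ − p₃) + nC(p₃ − p₁)]/N. With 88/79/70 (loss of 0, 10 and 20%):
- Mild: (−26.4 − 15.8 + 35)/237 = −0.030 SD, 10% of 0.297.
- Moderate: (−44 − 23.7 + 56)/237 = −0.049 SD, 17%.
- Large: (−88 − 39.5 + 105)/237 = −0.095 SD, 32%.

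Reversing the loss to 70/79/88 gives the same sizes with a positive sign. With 79/79/79 the terms cancel exactly. With week fitted, the bias is zero in every case.

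**Step 5: how far chance alone unbalances the sequences.** If everyone has the same 10% risk of dropping out, each completer count has variance 88 × 0.9 × 0.1 = 7.92. The SD of the bias is √(7.92 × Σc²)/237.6, where c is the set of three differences in step 4. Σc² is 0.38 for mild and 3.5 for large gains, so the SD is 0.007 to 0.022 SD.

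**Step 6: lettering.** The Abstract gives the sequences as ABC/BCA/CAB. Written with A for adequate, B for inadequate and C for none, the schedule under Participants and study design is ACB/BAC/CBA. The same letters therefore stand for treatments in one place and randomised groups in another, and the two sets of sequences differ. Both are period-balanced, so the conclusions on precision and on the need for a week term hold for either.

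**The case against.** The strongest defence has four parts.

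- **Counterbalancing already protects the estimate.** This stands for equal or evenly reduced sequences. There the omission costs power and does not raise the false-positive rate.
- **The practice gain is undocumented.** This stands as to size. The statement on test order concerns the order within the battery, and a common alphabet need not mean the same answer sheet, so parallel forms are not excluded. A gain over three weekly sittings of timed tasks remains plausible, and fitting week costs almost nothing if there is none.
- **The power loss may be harmless.** This stands if the effect is as large as planned and the cities are pooled (step 3). The lower figures apply to a smaller effect, about 0.30 SD with 237 completers, or to analysing each city alone. They still matter, because the Discussion claims power for relatively small effects.
- **An article condenses, and a fuller plan may fit week.** This stands only in part. The model's factors are stated outright, and the open-ended list concerns confounders, so as written the model has no period term.

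Two stronger readings are tempting. A reader might infer from the Group A/B/C gloss that the ANOVA compares randomised sequences and not breakfasts. The text does not support that: the factor is called breakfast condition, is within subjects, and is followed by comparisons between breakfast types, so this is a labelling inconsistency. A reader might also infer that the results will be biased or falsely positive. That needs sizeable practice gains and loss that depends on sequence together, and the dropout reasons listed (travel, tardiness, resignation) give no cause for the second. At 88/79/70, simulated pairwise rejection under the null stayed near nominal, at about 2%.

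**Conclusion.** The point holds as a weakness in the stated model that should be fixed; it is not a fatal flaw. If there is any practice gain, omitting week inflates the error variance: by factors of 1.06 to 1.58 over the assumed range. What that costs depends on the effect. Power falls from 80% to between 78% and 59% for an effect just detectable with 237 completers, but stays at 94% or more for the effect that 117 would detect, once the cities are pooled. Bias arises only if completers differ between sequences. It is 10 to 32% of the 0.30 SD detectable effect at 88/79/70, with either sign, and small under even dropout. All sizes rest on assumed gains and on complete-case analysis; the direction of the precision loss does not.

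**What to change.** Add week (three levels) as a fixed effect to the within-participant model. The simplest form is a linear mixed model in SAS with breakfast received that week, week, sex and sex-by-breakfast as fixed effects, a participant random effect, and every attended visit included. Take the three Bonferroni pairwise contrasts from it. A sequence term is optional: its main effect does not change within-person contrasts.

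Define the within-subject factor as the breakfast received (adequate, inadequate or none), keep separate labels for the randomised groups, and reconcile the lettering and sequences across the Abstract, Participants and study design, and Analysis strategy.

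The cost is two degrees of freedom and a few sentences of wording, with no new data. The change should be made before outcome data are seen.

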## Methods/Design

### Study hypothesis

Participants who eat a nutrition-adequate breakfast will have better cognitive performance than those who eat a nutrition-inadequate breakfast or do not eat breakfast.

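### The only multiplicity rule covers the three breakfast pairs, while one cognitive hypothesis can be tested on about nine scores, none named as primary, from a battery listed inconsistently

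*Protocol article*

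**What the plan says.** The Study hypothesis section of the protocol article gives a single hypothesis: "Participants who eat a nutrition-adequate breakfast will have better cognitive performance than those who eat a nutrition-inadequate breakfast or do not eat breakfast". It does not say on which measure.

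Under Analysis strategy, "Repeated-measures analysis of variance (ANOVA) will be used to examine cognitive function performance", with breakfast condition as the only within-subjects factor. For the overall test, "The significance level will be set at <0.05". Then "The Bonferroni adjustment method will be used to perform the pairwise comparisons across different breakfast types", and the resulting level is given as 0.01667, that is 0.05/3. All P-values are two-sided. No adjustment across cognitive scores, composite or order of importance among scores is given.

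The Cognitive function tests section confines the cognitive tests to three domains and fixes the weekly order as "1) Mood, (2) Hunger and satiety, (3) Short term memory, (4) Learning and memory, and (5) Attention". Later subsections go further. Attention ends by saying that the "correct number of tracking lines as measured by the Visual Tracking Test will be calculated". Creativity sets a further task: "Within 5 minutes, participants will be asked to list as many different items as possible that fit the above descriptions". Language logic defines two more results.

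**The concern.** The divisor of 3 is the number of breakfast pairs, so the adjustment works within one score. The hypothesis is worded for cognition as a whole, so as the text stands a significant result on any score could be offered in its support. The article chose a multiplicity rule and fixed its divisor, but the rule leaves out the larger source of multiplicity.

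The set of scores is itself unsettled, because different sections list different tests. A reader cannot tell which scores count as cognitive performance, and so cannot say how large the family of tests is. The Discussion section expects the results might move public health officials to act, so it matters that the claim rests on a measure fixed in advance.

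**Working it through.** **The plan's own figure.** 0.05/3 = 0.016667, which matches the stated 0.01667. For three conditions and one score, it holds the chance of any false-positive pair to about 4.4% (simulation below). The rule does what it says within one score.

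**Counting the scores**

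| Section | Scores | Number |
|---|---|---|
| Short-term memory | digit span total | 1 |
| Learning and memory | digit-symbol items correct in 90 seconds | 1 |
| Attention | reading velocity, mistake rate, index of mental capacity, tracking lines | 4 |
| Creativity | items listed (a count is implied, not stated) | 1 |
| Language logic | completed number, correct number | 2 |

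The total is nine, of which six fall in the three domains of the stated battery. It is ten if test time in the Attention section is read as its own score.

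**At least one false-positive overall ANOVA, independent scores,** 1 − 0.95^k:
- k = 6: 1 − 0.95^6 = 26.5%
- k = 9: 1 − 0.95^9 = 37.0%
- k = 10: 1 − 0.95^10 = 40.1%

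**Correlated scores and directional claims.** The article gives no correlations among scores, so an equal correlation ρ is assumed. The figures below come from a large-sample simulation (400,000 draws) of three conditions with no true difference. Pairs are tested two-sided at 0.05/3, so a false result in one given direction on one pair has probability 0.05/6 = 0.00833.

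| False result, nine scores | ρ = 0 | ρ = 0.3 | ρ = 0.5 | ρ = 0.7 |
|---|---|---|---|---|
| Any overall ANOVA below 0.05 | 37% | 33% | 27% | 21% |
| Adequate better than at least one comparator, on any score | 13% | 11% | 9% | 7% |
| Adequate better than both comparators, on the same score | 0.9% | 0.9% | 0.8% | 0.6% |

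For a single score, the second and third rows are 1.6% and 0.1%. For the six scores inside the stated battery, the second row is 9%, 8%, 7% and 6%.

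**A harder case for the both-comparators rule.** Suppose the adequate breakfast truly equals one comparator and the other is clearly worse on every score. A false claim on a score then needs only one directional error, with probability 0.00833. For independent scores:
- nine scores: 1 − (1 − 0.00833)^9 = 7.3%
- six scores: 1 − (1 − 0.00833)^6 = 4.9%

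**The battery, side by side**
- Abstract (Methods): short-term memory, attention, working memory.
- Cognitive function tests: attention, short-term memory, and learning and memory, in a fixed order.
- Creativity and Language logic: two further tests with no place in that order.
- Attention: scores a Visual Tracking Test, but the only task described is letter deletion.

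**The success rule.** The Study hypothesis joins the two comparators with *or*; the Discussion part of the Abstract joins them with *and*. Neither says whether both must be beaten on the same score.

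**The case against.** The strongest objection is that 37% is not the chance of wrongly supporting the hypothesis. The hypothesis is directional, whereas an overall ANOVA result includes the adequate breakfast doing worse, or the inadequate breakfast differing from none. That stands. A reader might infer from the nine scores that a false claim for the adequate breakfast has a 37% chance; the text does not support this. The directional figure is about 9% to 13% if beating either comparator suffices, and about 1% under no effect if both must be beaten.

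Second, the article does not say that each score has its own ANOVA or that one significant score is enough. This also stands. Separate testing is the natural reading, because breakfast condition is the only within-subjects factor and no composite or multivariate test is named, but it remains a reading. Nor does any section describe choosing a score after the data are seen; the text merely does not prevent it.

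Third, a condensed article may leave the choice of primary score to a full protocol or analysis plan that is not shown. The bare absence is therefore not the point. What remains is that the article fixes the divisor at 3 for a hypothesis spanning several scores, and that its own sections disagree on the tests. An unseen document cannot cure that disagreement.

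Finally, nine is a soft count, since three of the nine scores lie outside the stated battery and creativity has no scoring rule. The six-score figures are given for that reason, and they do not change the conclusion.

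**Conclusion.** The point holds as a gap in error control joined to a contradiction in the battery. The 0.05/3 rule is correct for the breakfast pairs and does not extend to the scores that could carry the hypothesis.

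How much this matters depends on a success rule that the article does not state. If beating either comparator on any score counts, the risk of a false claim rises from 1.6% to roughly 9% to 13%. If both must be beaten on the same score, it stays near 1% under no effect and reaches about 7% only in the harder case with nine independent scores. The 21% to 37% range describes any significant overall ANOVA and should not be quoted as the risk for the hypothesis.

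These sizes assume separate tests per score, the count of nine, and equal correlations that the article does not supply. The conflict among the test lists rests on no assumption.

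**What to change.** - In Study hypothesis and Analysis strategy, name one primary cognitive score, for example digit-symbol items correct in 90 seconds, or one composite defined in advance. Either would serve.
- State whether support requires the adequate breakfast to beat both comparators on that measure.
- Keep 0.05 for its overall test and 0.05/3 for its pairs. Treat the other scores as secondary with Holm adjustment across them, or label them exploratory.
- In the sample size section, say which score the reference values 36.6, 25.9 and 26.8 refer to. At present they belong to an unnamed cognitive performance value.
- Make the Abstract, Cognitive function tests, Attention, Creativity and Language logic sections list one identical battery, and either describe the Visual Tracking Test or remove its score.

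The cost is protocol wording, with no added participants. The downside is that secondary scores face a stricter threshold or support weaker claims. The alternative of spreading Bonferroni over all nine scores is dearer: the pairwise level becomes 0.05/27 = 0.00185, which cuts 80% power at 0.05/3 to about 55%, or needs about 1.49 times the sample to restore it.
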